## Abstract

**Background:**

Ageing is a process characterised by chronic low-grade inflammation and oxidative stress which could lead to increased prevalence of both physical and mental age-related chronic conditions. A healthy balanced diet, rich in fruit and vegetables as well as omega-3 polyunsaturated fatty acids (n3 PUFA), could reduce oxidative stress and improve markers of low-grade inflammation. Nonetheless, considering that a large part of the population struggles to meet current guidelines on fruit and vegetable and n3 PUFA recommendations, fruit and vegetable concentrate supplements and mixed omega fatty acid supplements could be an effective strategy to bridge the gap between actual and recommended intakes.

**Methods:**

In this randomised, controlled, open-labelled, parallel-grouped clinical trial, 112 participants will be allocated to one of four arms (*n* = 28 on each arm): an encapsulated juice powder concentrate, a plant-based omega fatty acid supplement, both or a control group. We aim to investigate whether long-term separate or combined ingestion of the two can affect biomarkers of cardiovascular health, low-grade inflammation and indicators of ageing, including cognitive function, in middle-aged and elderly people. We will additionally explore the effect of the different supplementations on plasma levels of vitamins, carotenoids and fatty acids. Intervention will last 2 years and participants will be assessed at baseline and at follow-up visits at 6, 12, 18 and 24 months.

**Discussion:**

This study will provide evidence whether long-term, plant-based dietary supplementation can support cardiovascular health, anti-inflammatory processes, immunity and nutritional status in ageing.

*Trial registration* This trial was registered at ClinicalTrials.gov (NCT04763291) on February 21, 2021.

## Background

The global elderly population has been growing exponentially in the last few years, and according to the World Health Organization, it is estimated that it will nearly double between 2015 and 2050 [1]. This results in an increased prevalence of age-related chronic conditions, including atherosclerosis and cardiovascular diseases (CVD), insulin resistance and type 2 diabetes, cognitive decline and diminished mental health [2]. Many of these conditions are interrelated. For example, ageing in blood vessels could not only lead to the development of vascular diseases, but could also affect the central nervous system, where cerebral vascular ageing could lead to cognitive decline [3].

Dietary intake is a modifiable risk factor that could affect the incidence and severity of age-related functional decline and prevalence of the aforementioned age-related diseases. Evidence from previous epidemiological studies supports a strong relationship between fruit and vegetable consumption and reduced cardiac risk [4, 5]. This could be mediated via improvements in blood pressure, platelet function and vascular reactivity; yet, the mechanisms of protection are not clear. Increased fruit and vegetable consumption has also been associated with reduced inflammation and enhanced immune cell profile, according to a recent systematic review and meta-analysis [6]. Some epidemiological studies have reported that fruit and vegetable intake is inversely associated with proinflammatory biomarkers, such as C-reactive protein (CRP) [7] and tumour necrosis factor alpha (TNF-α) [8]. In addition, inflammation is closely related to oxidative stress, and since one process can easily induce the other, they are often found together in many pathological conditions [9]. It is known that certain vitamins and polyphenols found in fruits and vegetables protect against oxidative stress by scavenging free radicals [10, 11]. Vitamin C, for instance, reduces cellular oxidative stress and improves endothelial function [10]. Vitamin E, another potent antioxidant, has been shown to decrease lipid peroxidation and improves endothelial function by increasing plasma nitric oxide [11]. Beneficial effects have also been observed for higher fruit and vegetable intake—and consequently antioxidants—and cognitive health, including age-related cognitive impairment [12]. This is achieved by the antioxidant and anti-inflammatory activities of these compounds and their ability to improve cellular signalling and neuronal communication [13].

Previous studies have also demonstrated the importance of long-chain omega-3 fatty acids on humans’ health and their positive effects on the cardiovascular system and blood lipids regulation [14, 15]. Long-chain omega-3 polyunsaturated fatty acids (n3 PUFA) are also considered to have anti-inflammatory effects [2], and increased long-chain n3 PUFA intake has been associated with reduced circulating levels of pro-inflammatory cytokines in the elderly [16]. The n3 PUFA eicosapentaenoic acid (EPA) and docosahexaenoic acid (DHA) are essential fatty acids that humans are not able to synthesise, and hence have to be supplied through the diet [15].

Dietary patterns with adequate intake of fruit and vegetables, micronutrients and n3 PUFA can reduce oxidative stress and improve markers of low-grade inflammation, cardiovascular risk profile and cognitive function [17–22]. According to the Austrian nutrition report and the Austrian Health survey, Austrian adults consume on average two out of the five recommended portions of fruit and vegetables per day [23] and only half of the population consumes one portion of fish per week, with the remaining half consuming lower amounts [24]. Similar patterns are observed in other western countries [25, 26]. Considering that many people’s fruit and vegetable and n3 PUFA intakes are below recommendations, supplementation with fruit and vegetable concentrates and mixed omega fatty acid supplements could potentially exert beneficial effects on their health. Previous short-term studies have shown that supplementation with fruit and vegetable concentrates is able to reduce low-grade inflammation and oxidative stress in different cohorts of people [27, 28]. Little is known though about the effect of such supplements over the long term. The aim of this study is to investigate whether long-term separate ingestions of an encapsulated juice powder concentrate or a plant-based omega fatty acid supplement, or a combined ingestion of the two, can affect biomarkers of cardiovascular health, low-grade inflammation and indicators of ageing in middle-aged and elderly people.

## Methods

### Study design

This is a randomised, controlled, open-label, parallel-grouped clinical trial. Enrolled participants will be stratified by gender and randomly allocated to one of the following arms:Control group (no intervention)Fruit, Vegetable and Berry (FVB) group, where participants have to ingest an encapsulated fruit, vegetable and berry juice powder concentrate.Omega group, where participants have to ingest an encapsulated plant-based fatty acid supplement.Fruit, Vegetable, Berry and Omega (FVBO) group, where participants have to ingest the fruit, vegetable and berry supplement, together with the plant-based fatty acid supplement.

Randomisation will be performed by a true random number service that generates randomness via atmospheric noise (‘RANDOM.ORG’, Randomness and Integrity Services Ltd., Dublin, IE), by an independent statistician not involved in the recruitment process or analysis of data. In order to ensure a balanced sample size across groups over time, we will stratify by gender and perform block randomisation with a block size of 4. Allocation concealment will be ensured, as the independent statistician will only release the randomisation code to the study team, after a participant is fully enrolled in the study.

The intervention will last 24 months and participants in all groups are advised to continue their habitual diet and lifestyle, throughout the whole duration of the study.

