### Study visits and procedures

#### Screening visit

Subjects expressing interest to participate in the study will be invited to a screening visit. On the screening visit, a research team member will go through the participant information sheet and explain all study procedures to potential participants. Participants will have the opportunity to ask any questions they might have. If they are still interested to participate, they will be asked to sign an informed consent form, prior to any measurements being taken.

During the screening visit, participants’ medical history will be assessed and measurements of height, weight, BMI and blood pressure (BP) will be taken. Participants meeting the inclusion criteria will be enrolled in the study and an appointment for the baseline visit will be arranged. A minimum of 6-week washout period, to eliminate any interfering nutritional supplements and dietetic products, will be allowed between the screening and baseline visit. Also, in order to avoid a potential effect of physical activity and changed nutritional habits on the measured blood markers, participants will be asked to abstain from any form of strenuous physical activity and complete an estimated food diary, 4 days prior to the baseline visit. Detailed information on how to complete the food diary will be provided during the screening visit.

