At the end of the baseline visit, participants will be randomly allocated to one of the four groups. Participants in the control group will continue with their habitual diet and lifestyle. Those allocated to the three whole food supplement groups, will have to continue their habitual diet and lifestyle, and will also be provided with the corresponding supplements they will have to ingest. Participants will be asked to avoid disposing of any unused capsules and return any leftovers in the next follow-up visit. In addition, all participants will receive a copy of the Wisconsin Upper Respiratory tract Symptoms Survey (WURSS-21) and the Gastro-Intestinal Symptoms Survey-16 (GISS-16) and will be asked to fill these in every time they experience upper respiratory tract or gastrointestinal symptoms, during the duration of the intervention. They will also be reminded that over the following two years they will have to maintain their habitual diet which must correspond to the nutritional inclusion and exclusion criteria.

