#### Sample size

The sample size calculation was performed according to omega-3 index changes as a key biomarker of cardiovascular health and TNF-α changes as a key biomarker of low-grade inflammation, following supplementation. Assuming a two-tailed t-test using 5% significance level (two-sided), a sample size of 18 and 19 subjects per group was determined to have 80% power to detect a 30% increase on omega-3 index [32] and a minimum decrease of 0.4 ng/L on TNF-α [43], respectively. Allowing for a dropout rate of 30% over 24 months, we aim to recruit 112 participants in total (*n* = 28 control group; *n* = 28 FVB group; *n* = 28 Omega group; *n* = 28 FVBO group).

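### A single fixed block size of 4 across four open-label arms makes the last allocation of each block inferable, so the concealment claim is too strong

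*Protocol article*

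**What the plan says.** The Study design section describes the trial thus: "This is a randomised, controlled, open-label, parallel-grouped clinical trial". There are four arms, one of them a no-intervention control, and on allocation the section says "we will stratify by gender and perform block randomisation with a block size of 4". No other block size is mentioned. Under Sample size, "we aim to recruit 112 participants in total", with 28 per arm, so the ratio is 1:1:1:1.

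Study design rests concealment on one safeguard: "the independent statistician will only release the randomisation code to the study team, after a participant is fully enrolled in the study".

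Three other sections bear on timing. Under Screening visit, "Participants meeting the inclusion criteria will be enrolled in the study and an appointment for the baseline visit will be arranged", and the same section adds "A minimum of 6-week washout period, to eliminate any interfering nutritional supplements and dietetic products, will be allowed between the screening and baseline visit". Under Baseline visit, the study physician reviews the history again against the inclusion criteria, and the food diary is collected and checked against the fruit and vegetable limit. The same section then says "At the end of the baseline visit, participants will be randomly allocated to one of the four groups", and supplements are handed out at that point.

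**The concern.** Withholding the code protects an allocation only if it cannot be worked out from earlier ones. With as many arms as places in the block, it can be. The trial is open-label and all visits after screening take place at one centre, so staff there see what each participant receives. Once three people of one gender in a block have been assigned, the fourth arm is the one left over.

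The route to bias is the baseline visit. The eligibility review and the food-diary check come before allocation and involve judgement. Someone who can infer the next arm could, even without intent, apply those checks more or less strictly. In a trial with no blinding of participants or staff and no placebo, concealment is one of the main remaining protections against selection, so it should not be claimed beyond what the method delivers.

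**Working it through.** **Inputs.** Four arms, open-label, strata by gender, block size 4 (Study design); 19 evaluable per group for TNF-α, 30% dropout, 112 in total, 28 per arm (Sample size). The gender split is not given; where one is needed, 56 per gender is assumed.

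**Plan's own figure.** 19 / (1 − 0.30) = 27.1, rounded up to 28; 28 × 4 = 112. This reproduces. The number of blocks is 112 / 4 = 28.

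**Certain allocations, block of 4.** Each arm appears once, so exactly one place per complete block, the last, is certain: 28 of 112 = 25%. If the gender counts are not multiples of 4, there are 27 complete blocks.

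**Best-guess rate, block of 4.** The chance of a correct guess at places 1 to 4 is 1/4, 1/3, 1/2 and 1.
- Sum per block: 1/4 + 1/3 + 1/2 + 1 = 25/12 = 2.083
- Rate: 2.083 / 4 = 52.1%, or 58.3 of 112
- Pure chance: 25%, or 28 of 112

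**Larger blocks.** In a block of 4m with each arm m times, the expected number of certain places is the expected length of the closing run of one arm.
- Block of 8 (m = 2): 1 + 4 × (2×1)/(8×7) = 1.143, and 1.143 / 8 = 14.3%
- Block of 12 (m = 3): 1 + 4 × (3×2)/(12×11) + 4 × (3×2×1)/(12×11×10) = 1.2, and 1.2 / 12 = 10.0%

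Best-guess rates come from exact enumeration for known fixed sizes with complete blocks, and from simulation for hidden sizes (56 per gender, guessing the arm least used so far):

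| Scheme | Certain | Best guess correct |
|---|---|---|
| Fixed 4, known | 25% | 52.1% |
| Fixed 8, known | 14.3% | 47.0% |
| Fixed 12, known | 10.0% | 44.1% |
| Random 4/8, hidden | block boundary unknown | about 48% |
| Random 8/12, hidden | block boundary unknown | about 44 to 45% |

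With 56 per gender the last block of 12 is incomplete, and the simulated rate for fixed 12 falls to about 43%.

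Two things follow. With four equal arms, 4 is the smallest balanced block and so the most predictable. And hiding the sizes mainly removes certainty. It does not push the guess rate below that of a known fixed block of 12, because guessing the least-used arm needs no knowledge of the block size.

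**Timing passages side by side.** Screening visit uses enrolment for people who pass screening, at least 6 weeks before baseline. Study design ties code release to full enrolment, which it does not define. Baseline visit puts allocation at the end of that visit. Adherence to the 6-week washout is itself an inclusion criterion and can only be established after screening, so full enrolment is most naturally read as completed at baseline.

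**The case against.** The strongest reply is that exploiting the pattern takes knowledge of the size, an accurate tally by gender, and a chance to act. The block size stands in the team's own article, but the documents do not say whether recruiting staff knew it, or whether it was public, during recruitment. Screening takes place at a different institute, and the baseline appointment is arranged at least 6 weeks ahead, when the future position within a block is generally unknown. This stands: the opening narrows to the baseline checks or a rescheduled visit, and 25% and 52% are upper limits. It does not restore the safeguard, because withholding the code has no bearing on inference from assignments already seen.

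Three stronger readings are tempting and not supported:
- A reader might infer from the enrolment wording that the arm is to be disclosed after screening. The Baseline visit section states the allocation time explicitly, and full enrolment can be read consistently with it. This is loose wording, not a plan to unmask.
- A reader might infer that baseline quality-of-life answers or cognitive performance would be distorted. Nothing suggests that participants know the block size or past assignments. The cognitive test is electronic and scored automatically, and both measures are secondary outcomes.
- A reader might infer that staff could book visits in a chosen order to steer allocation. The documents do not describe this.

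**Conclusion.** The point holds in a limited form. A single fixed block of 4 for four equal open-label arms leaves up to 28 of 112 allocations (25%) certain and allows a best guess that is right 52% of the time, about twice chance. This assumes that blocks complete and that staff know the size and track assignments perfectly within gender. Because the inference is possible before the baseline eligibility and food-diary checks, the article should not say that withholding the code assures concealment. Nothing in the documents shows that allocation was subverted, and the sample size is unaffected. The enrolment and allocation wording is a separate matter of clarification only. This is a change the plan should make, not a fatal flaw.

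**What to change.** 1. **If allocations remain.** Have the independent statistician produce a new list for the remaining places, using permuted blocks of randomly varying size (for example 8 and 12) within gender, with the sizes withheld from the study team. This largely removes certain allocations and lowers the best-guess rate from 52% to about 44 to 45%. The cost is one new list and arms that may differ by a few participants per gender when recruitment stops (at most 3 between largest and smallest arm in the simulation with 56 per gender).
2. **If recruitment is complete.** A new list serves no purpose. Soften the concealment statement, report the fixed block size of 4 as a limitation, and state when each assignment was in fact released.
3. **Wording, in either case.** Reconcile Study design, Screening visit and Baseline visit with one sentence: each single assignment is released only after the baseline eligibility review, food-diary check, blood draw, cognitive test and questionnaires are complete. This costs nothing beyond the edit.

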### Recruitment and trial setting

Participants will be recruited from the Graz area, Austria, either by word of mouth or by replying to advertising material such as leaflets placed in public places including gyms, medical practices, pharmacies, seniors’ associations and clubs or via social media announcements.

Screening visits will take place at the Greenbeat Institute of Nutrient Research and Sports Nutrition. All remaining visits will take place at the Otto Loewi Research Center, Division of Medicinal Chemistry of the Medical University of Graz, Austria.

### Participants

#### Inclusion criteria

Males and femalesAge: 55–80 yearsPost-menopausalNon-smokersBody mass index (BMI): 18.5–40 kg/ m^2^Fruit and vegetable intake: ≤ 4 servings/ dayAdherence to a 6-week washout period, for dietary supplements not ingested for specific medical conditions.

#### Exclusion criteria

Age: < 55 and > 80 yearsSmokers (or ex-smokers who quit smoking < 3 years ago)Aversion to stop the intake of multivitamins, multiminerals or omega fatty acid supplementsSubjects with histamine intoleranceHypertension, starting with grade 2 according to the classification of the European Society of Hypertension (systolic blood pressure > 160 mmHg; diastolic blood pressure > 100 mmHg)All medication taken for less than 3 months or with changes on the dosage over the last 3 monthsMedication for any of the conditions listed belowClinically relevant infectious diseasesAll forms of dementia and Alzheimer’s diseaseDiabetes mellitus type I and type IIAutoimmune diseasesStents and cardiovascular diseasesCancer patientsPregnancySignificant lifestyle changes, e.g. changes in diet and physical activity profile

### Interventions

#### Encapsulated fruit, vegetable and berry juice powder concentrate

The encapsulated fruit, vegetable and berry juice powder concentrate (Juice Plus + ®capsules) is a vitamin- and phytonutrient-rich supplement, derived from 36 dried fruits, vegetables and berries. Participants in the FVB and FVBO groups will be asked to ingest 6 capsules per day, which provide 2910 µg β-carotene, 158mg vitamin C, 18.2mg α-tocopherol equivalents (α-TE, vitamin E), 316 μg folic acid, 6.1mg lutein, 1mg lycopene, > 100 different phenolic compounds and approximately 600mg of polyphenols [29]. Table 1 provides detailed information on the recommended daily allowance (RDA)/ adequate intake (AI)—for available nutrients—contained in the FVB capsules as well as the % RDA/ AI covered by the ingestion of 6 capsules per day, based on the nutrient reference values for the DACH region (collaboration between the German, Austrian and Swiss nutrition societies) [30].

**Table 1 Tab1:** Nutrient reference values and % coverage offered by FVB and Omega capsules

Nutrient	Gender and age range	DACH/EFSA RDA/ AI	FVB (6 capsules)	DACH % RDA/ AI covered by FVB capsules (%)	Omega (2 capsules)	EFSA % AI covered by Omega capsules
β-carotene*	M; 51–65 years	10,200 μg	2910 μg	28.5	–	–
	M; > 65 years	9600 μg	2910 μg	30.3	–	–
	F; > 51 years	8400 μg	2910 μg	34.6	–	–
Vitamin C*	M	110 mg	158 mg	143.6	–	–
	F	95 mg	158 mg	166.3	–	–
α-tocopherol**	M; 51–65 years	13 mg	18.2 mg	140	–	–
	M; > 65 years	12 mg	18.2 mg	151.2	–	–
	F; 51–65 years	12 mg	18.2 mg	151.2	–	–
	F; > 65 years	11 mg	18.2 mg	165.5	–	–
Folic acid*	M & F	180 μg	316 μg	175.6	–	–
EPA + DHA**	M & F	250	–	–	275	110%

*AI* adequate intake, *DACH* Germany, Austria, Switzerland, *DHA* docosahexaenoic acid, *EFSA* European Food Safety Authority, *EPA* eicosapentaenoic acid, *F* female, *FVB* fruit, vegetable and berry, *M* male, *RDA* recommended dietary allowance

*Presented as recommended dietary allowance (RDA)

**Presented as adequate intake (AI)

#### Encapsulated plant-based fatty acid supplement

The encapsulated fatty acid supplement (Juice Plus + ®Omega Blend) contains plant-based omega fatty acids from algae (*Schizochytrium sp.*) and a variety of seed oils. Participants in the Omega and FVBO groups will be asked to ingest two capsules per day, which provide 375mg of n3 fatty acids [175 mg of DHA, 100mg of EPA, 55mg of docosapentaenoic acid (DPA) and 35mg of α-linolenic acid (ALA)], 250mg of n5 and n7 fatty acids, and 250 mg of n6 and n9 fatty acids. Table 1 provides information on the adequate intake (AI)—for available nutrients—contained in the Omega capsules as well as the % AI covered by the ingestion of 2 capsules per day, based on the nutrient reference values from the European Food Safety Authority (EFSA) [31].

Based on previous experience and in order to increase tolerability, participants are recommended to take capsules with a meal, preferably in the morning and evening. Previous studies have tested the safety of the supplements used and reported no effects on liver, kidney and thyroid function [32, 33].

